## Supplement 1. Study Protocol

# Title: Self-administered Acupressure for Knee Osteoarthritis in Middle- and Older-Aged Adults: A Randomized Controlled Trial

## Abstract

**Objectives:** To evaluate the short- and medium-term effectiveness of self-administered acupressure taught by a short training course on reducing knee osteoarthritis (OA) pain in middle-aged and older adults.

**Hypothesis:** The self-administered acupressure group would have a greater pain relief compared to the knee health education (KHE) control in subjects with knee OA at week 12 (medium-term).

**Design and subjects:** In this fully-powered randomized controlled trial, 314 participants with knee OA recruited from the community will be randomized to self-administered acupressure or KHE group in a 1: 1 ratio.

**Study instrument:** Numerical rating scale (NRS) will be used to assess pain intensity in the knee.

**Interventions:** Participants in the self-administered acupressure will attend two 2-hour training sessions (1 week apart) to learn self-administered acupressure and practice twice daily for 12 weeks. Participants in the control group will receive knee health education of the same schedule and duration.

**Main outcome measures:** The primary outcome measure is the NRS score at 12 weeks. Other outcomes include Western Ontario and McMaster University Osteoarthritis Index, Short Form Six Dimensions, Timed Up & Go Test, Fast Gait Speed, pain medication usage. Compliance of self-administered acupressure will also be evaluated.

**Data Analysis:** Differences in the scale scores and test parameters will be examined using a linear mixed-effects model.

**Expected results:** Subjects in the self-administered acupressure group will have greater improvement in NRS and other related parameters compared to those in the KHE group at week 12.

## 1. Introduction

Knee osteoarthritis (OA) is a debilitating condition that commonly affects people aged over 50 years and 16% of people aged 45 or above were influenced (1). Acupuncture is well-evidenced for the effective treatment of knee OA pain (5); whereas acupressure, a non-invasive variant of acupuncture, is relatively less researched. Acupressure stimulates the same acupoints as acupuncture with the use of fingers, hands, or elbow based on traditional Chinese medicine (TCM) meridian theory. To facilitate a timely and more frequent intervention, acupressure can be self-administered by patients with knee OA after proper training, so that they may perform the acupressure after waking up in the morning or after a long walking in which the pain is usually more prominent.

We conducted a pilot RCT to test the feasibility and explore the effects of the self-administered acupressure on empirical acupoints to relieve knee OA pain using knee health education as a control from May to August 2017 (ClinicalTrials.gov identifier: NCT03155737). The subjects received either two lessons of self-administered acupressure training (n=17) or knee health education (n=18). They were phoned twice per week to remind their practice and answer queries during the 6-week study period. All subjects in the self-administered acupressure group had learned the self-acupressure technique and passed fidelity check after the course; the compliance was good (15 out of 17 subjects had attended all lessons). 83.3% of them had practiced the acupressure 5 days or more per week during the 6-week study period. The self-administered acupressure group showed a mean reduction of 2.27 points (SD=1.2) in NRS of pain scale and the total score appeared to be lower than the knee health education group ( $d=0.49$ ), though they were not statistically significant due to the small sample size.

## 2. Aims and Hypotheses:

We hypothesize that the self-administered acupressure group would have a greater pain relief compared to the knee health education control in subjects with knee OA at week 12 (medium-term).

The specific aims are:

1. To examine the short- and medium-term effectiveness of self-administered acupressure taught by a short training course on relieving knee OA pain in middle-aged and older adults.
2. To evaluate the subjects' compliance with self-administered acupressure for knee OA.

To achieve these aims, we will perform an RCT on self-administered acupressure for alleviating knee OA pain delivered through a short training course using a knee health education course as a control.

### 3. Subjects

This RCT will recruit 314 participants from the community through advertisement in community centres, radio Health Programme, and newspapers as well as mass email at the University of Hong Kong and the Hong Kong Polytechnic University. Interested participants who provide written informed consent will be further examined for inclusion and exclusion criteria by a trained research assistant.

Inclusion criteria: 1. ethnic Chinese; 2. aged 50 years or above; 3. ability to comprehend Chinese; 4. fulfilling any 3 of the following criteria: i. morning stiffness  $\leq 30$  min; ii. crepitus on active joint motion; iii. bone tenderness; iv. bone enlargement; or v. no palpable joint warmth (This classification yielded 84% sensitivity and 89% specificity for OA knee diagnosis (14)); 5. having knee pain for at least 3 months (15); 6. Knee pain  $\geq 3$  on a Likert pain scale from 1–10; 7. having a smartphone (or a family member living together having a smartphone) that is compatible to WhatsApp (it is our experience in the pilot study that most of every subject had been used to using WhatsApp for social communication); and 8. willing to provide informed consent.

Exclusion criteria: 1. medical diagnoses or conditions that preclude individuals from active participation (e.g. bleeding disorders, alcohol or drug abuse); 2. knee pain related to other conditions (cancer, fracture, rheumatoid arthritis, rheumatism) as screened according to the red flags for further investigation or referral in the NICE 2014 Guidelines for Osteoarthritis of the knee (16); 3. score  $< 22$  in Hong Kong Montreal Cognitive Assessment (HK-MoCA) indicating cognitive impairment that may prevent understanding of training instructions (17); 4. body mass index over 30, the obese II criteria for Asians (18) (it will be too difficult for the obese subjects to perform acupressure on the acupoints as physical pressure reaching the muscle is required); 5. presence of skin lesions or infections at the treatment sites; 6. ever had knee replacement surgery; 7. pregnancy or contemplating pregnancy, and 8. ever received acupressure or steroid injection for knee pain over the past 6 months.

Further investigation or referral, either at the screening or during the study, will be made when necessary. The CoA, a registered physiotherapist with a Master degree in Musculoskeletal Medicine and Rehabilitation and over 10 years clinical experience, will provide coaching in the screening and provide clinical opinions if necessary.

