### Treatment protocol

#### *Self-administered acupressure treatment group*

Participants in this group will receive two acupressure training sessions (2 hours each, 1-week apart). The self-administered acupressure treatment protocol was developed based on TCM meridian theory by the previous studies (10, 11) and modified by the PA who is an experienced acupuncturist. The acupoints are indicated for knee pain and have been commonly used (13). The protocol was tested for feasibility in our pilot study. We have modified the treatment protocol after the pilot study to further enhance the effectiveness and compliance of acupressure, including sending video on steps of locating acupoints and technique of acupressure to the participants via WhatsApp and incorporating a brief knee health education in the second session.

During the **1st session** (initial training), each participant will then receive a handout and an acupressure logbook. The handout includes a picture-illustrating acupressure step-by-step protocol. The acupressure logbook is for them to record their acupressure practice every day. The instructor will give a brief introduction about acupressure (20 minutes), followed by a group training on locating acupoints and manipulating acupressure technique (30 minutes). The treatment protocol consists of 4 steps (10, 11), namely warm-up, acupressure (on acupoints ST34, ST35, ST36, SP9, SP10, GB34, EX-LE2, and EX-LE4), rubbing the knee, and move the knee. The acupressure exercise takes about 16 minutes. The participants will then practice the acupressure (30 min), and then the instructor will inspect their performance of acupressure using a

competency checklist (30 minutes). The instructor will give feedback to their practice. Finally, the instructor will give a summary and answer queries (10 min). Additional training and practice time may be given to those who have not met the requirement in the checklist.

Participants will be asked to perform the acupressure exercise at home in the morning (within 1 hour after wake up) and night (within 1 hour after dinner) every day for 12 weeks. Participants will receive 2 follow-up phone calls from the instructor during the first week to remind their practice and answer their queries.

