#### Fidelity of self-administered acupressure in participants

The capability of participants for self-administered acupressure will be inspected by the instructor with a **competency checklist** in each session. The practice of self-administered acupressure will be assessed in four domains: accuracy of locating acupoints, acupressure technique, strength, and frequency of acupressure at each acupoint. Advice and correction will be made when necessary. Video on steps of locating acupoints and instruction on the technique of acupressure will be sent to the participants via WhatsApp for their reference at home. A contact phone number will be available for participants to contact the research assistant if they have any queries regarding the acupressure. Participants' acupressure technique will be assessed again at week 4.

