#### Methods of randomization and allocation concealment

Block randomization with a random block size of 4 to 6 will be used to randomize eligible participants equally into the two groups. A computer-generated list of numbers known only to an independent administrator will be used in the randomization process. The group allocation will be enclosed in sequentially numbered opaque sealed envelopes. After the participants have finished all baseline assessments and the blinded assessor has confirmed their eligibility, then the independent administrator will give the participants a sealed envelope. The participants will then open the envelope to reveal their group allocation. The research assistant who is responsible for phone-call follow-up will then look at their opened envelopes to log the participants' code and allocation.

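### No one-per-household limit with individual randomisation: cohabiting participants can be split between arms, bringing the trial's acupressure materials into a control's home before week 12 (cheap improvement, low severity)

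*Protocol*

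**What the plan says.** **Eligibility (Protocol, 3. Subjects).** Inclusion item 7 asks for "having a smartphone (or a family member living together having a smartphone) that is compatible to WhatsApp". Recruitment is by "advertisement in community centres, radio Health Programme, and newspapers", and by mass email at two universities. There are eight exclusions. The closest to this point is the last, "ever received acupressure or steroid injection for knee pain over the past 6 months", which looks only backwards from entry. None concerns a household member who is also in the trial, or a shared number.

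**Allocation (Methods of randomization and allocation concealment).** The unit is the individual: "Block randomization with a random block size of 4 to 6 will be used to randomize eligible participants equally into the two groups". Envelopes are handed out person by person: "The participants will then open the envelope to reveal their group allocation". No household unit is mentioned.

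**What goes home with the acupressure arm.** Under Self-administered acupressure treatment group: "The handout includes a picture-illustrating acupressure step-by-step protocol". Under Fidelity of self-administered acupressure in participants: "Video on steps of locating acupoints and instruction on the technique of acupressure will be sent to the participants via WhatsApp". Practice is at home, morning and night, for 12 weeks.

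**What controls are meant to receive.** Under Knee health education control group, controls are offered the same acupressure training as compensation, but only once the 12-week assessment is done. The primary outcome is the NRS at week 12, so controls are meant to be untrained up to the primary endpoint.

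**The concern.** The intervention is a home routine of about 16 minutes that can at least partly be copied from pictures and a video. Advertising in the community can bring in couples or relatives aged 50 or above together. If such a pair is split, the trial itself places the instructions in the control's home during the 12 weeks in which the design wants that person untrained. This differs from a control seeking acupressure elsewhere, because the sponsor can prevent it through its own eligibility rule.

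At stake is dilution of the week-12 NRS difference and some loss of the planned 90% power. Analysis cannot undo the exposure. It might also go unseen, since no assessment described in the protocol asks controls whether they used acupressure. The point belongs in the protocol rather than in a statistical analysis plan, because eligibility and the unit of allocation are fixed there.

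**Working it through.** **1. Reproduce the plan's sample size.** Inputs from Sample size calculation: standardised effect 0.40, power 90%, significance level 0.05 (sidedness not stated), attrition 15%.
- A two-sided two-sample t-test needs 132.3 per group, rounded up to 133. This matches. A one-sided normal approximation gives 108, which does not.
- Attrition: 133 / 0.85 = 156.5, so 157 per group and 314 in total. This matches.
- Power with 133 per group at d = 0.40 is 90.1%, so there is almost no reserve at the planning effect.

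**2. Number of exposed controls.** Let *h* be the share of participants enrolled as cohabiting pairs and *s* the share of pairs that split. Each split pair contains one control, so the exposed share of controls is *c* = *h* × *s*. The documents give neither quantity. Assumed: *h* = 5%, 10% or 20%, and *s* = 0.5.
- *h* = 5%: *c* = 2.5%, and 157 × 0.025 = 3.9 controls
- *h* = 10%: *c* = 5%, and 157 × 0.05 = 7.9 controls
- *h* = 20%: *c* = 10%, and 157 × 0.10 = 15.7 controls

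**3. Diluted effect and power.** If exposed controls gain a fraction *g* of the treatment effect, the expected difference is 0.40 × (1 − *c* × *g*), taking the SD as unchanged. Power is for a two-sided t-test at 0.05 with 133 per group.

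| *h* | *c* | d, *g* = 1 | Power, *g* = 1 | d, *g* = 0.5 | Power, *g* = 0.5 |
|---|---|---|---|---|---|
| 0 | 0 | 0.400 | 90.1% | 0.400 | 90.1% |
| 5% | 2.5% | 0.390 | 88.7% | 0.395 | 89.4% |
| 10% | 5% | 0.380 | 87.0% | 0.390 | 88.7% |
| 20% | 10% | 0.360 | 83.3% | 0.380 | 87.0% |

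**4. Sensitivity to *s*.** In a balanced block of 4, two relatives who fall in the same block split with probability 2/3; in a block of 6, with probability 3/5. Taking *s* = 2/3 for every pair and *g* = 1 gives power of 88.1%, 85.9% and 80.4% for *h* = 5%, 10% and 20%. This upper case applies only if every pair falls within one block of 4.

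**The case against.** **The phone clause is not an error.** Item 7 is a rule about access to a device. The relative who owns the phone need not have knee pain, be 50 or above, or enrol. The same item adds that, in the pilot, most participants were used to WhatsApp, so two participants on one phone would be uncommon. This stands. The gap is the absence of a household limit; the clause only shows that shared homes and phones were foreseen.

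**The size is assumed, and full effect is the extreme.** Acupressure participants get two 2-hour taught sessions, competency checks with correction, instructor calls in the first week, twice-weekly reminders and a week-4 technique check. A control who sees a handout or video gets none of the acupressure teaching. This stands, which is why the half-effect column matters. The promise of training after week 12 may also lessen the wish to copy early.

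**The effect size was already discounted.** The plan lowers the pilot's 0.49 to 0.40. Ten per cent full contamination of 0.49 leaves 0.49 × 0.90 = 0.44, with power of about 95%. This stands only in part: the discount is offered as general caution about a 35-person pilot, and using it for contamination spends it.

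**Correlated outcomes.** A reader might infer that ratings within a household are correlated and that treating them as independent overstates precision. Individual randomisation does not support this. Same-arm pairs raise the variance of the group difference and split pairs lower it. With 20% of participants in pairs and an assumed correlation of 0.3, simulation gives a variance ratio of about 0.99 against independence. The analysis model's detail may in any case sit in a statistical analysis plan that is not shown.

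**Conclusion.** The point holds as a gap in what the protocol permits. Nothing in the eligibility criteria or the allocation procedure stops two cohabitants from being split, and the trial's own materials would then enter a control's home before the primary endpoint.

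A reader might infer that the control arm is contaminated by design. The documents do not support that. Two eligible cohabitants would have to enrol, be split, and the control would have to take up the practice. Any resulting bias is toward no difference, so it cannot create an apparent benefit.

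The loss is probably small: about 1 to 3 percentage points of power if 5% to 10% of participants enrol as pairs, and about 7 points if 20% do and exposed controls gain the full effect. These figures rest on assumed pair shares, on half the pairs splitting, and on the plan's 0.40 being the true effect. This is a cheap improvement of low severity.

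**What to change.** Add one exclusion to section 3 of the protocol: *living in the same household as, or sharing a WhatsApp number with, a person already randomised in this trial*. Check it at screening by asking about address and number. The rule depends only on whether the other person has been randomised, not on their arm, so it leaves allocation concealment intact. The target of 314 does not change.

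The cost is one line, one screening question and the loss of a few otherwise eligible second household members.

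Giving both household members the same allocation and fitting a household effect is not a good substitute. It makes every pair a same-arm cluster: with 20% in pairs and a correlation of 0.3 (both assumed), the variance rises by a factor of about 1 + 0.20 × 0.3 = 1.06. It would also reveal a later-joining member's arm before enrolment, whereas the protocol reveals allocation only after baseline assessment and confirmed eligibility.

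### Exclusion 8 screens for recent acupressure but not for earlier training in it, so people who already know the technique can be eligible for either arm

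*Protocol*

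**What the plan says.** Exclusion 8 (Protocol, section 3, Subjects) removes people who "ever received acupressure or steroid injection for knee pain over the past 6 months". No other criterion in that section mentions acupressure, earlier training in it, or the pilot trial. Recruitment is open: "This RCT will recruit 314 participants from the community through advertisement in community centres", together with radio, newspapers and university mass email.

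The intervention is a skill that participants learn. Section 1 (Introduction) says that "acupressure can be self-administered by patients with knee OA after proper training", and aim 1 in section 2 asks about effectiveness when the technique is taught in a short course. Section 1 also describes a pilot, run from May to August 2017, in which 17 people were trained: "All subjects in the self-administered acupressure group had learned the self-acupressure technique and passed fidelity check after the course".

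The control-group description (Knee health education control group) offers controls the acupressure training only once the 12-week assessment is complete. Routine care is allowed in both arms (Concomitant treatments), and nothing tells controls not to use acupressure.

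**The concern.** A look-back window suits a treatment whose effect wears off, such as an injection. It does not screen for knowledge of a technique. Someone trained a year ago who has since lapsed passes exclusion 8 on its more natural reading, yet already has what the protocol withholds from controls until after week 12.

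The wording adds a second problem. *Ever* and the 6-month limit pull in opposite directions, and *received* leaves self-administration open. Two screeners could decide differently about the same former trainee.

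Two things are at stake. In the control arm, trained people who practise would shrink the week-12 NRS difference, and the intention-to-treat analysis keeps them in that arm. In the acupressure arm, people who already know the technique make it harder to attribute the result to the two training sessions, which is the subject of aim 1.

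**Working it through.** **Eligibility, criterion by criterion.** A former trainee can enter if three conditions all hold:

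- item 8 is read as a 6-month window on acupressure;
- more than 6 months have passed since their last acupressure, or the screener does not count self-administration as received;
- they meet every other criterion, including knee pain of at least 3 "on a Likert pain scale from 1–10".

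For pilot trainees, six months after August 2017 is about February 2018. The protocol gives no recruitment dates for the main trial, so the documents do not settle whether this condition is met.

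**Reproducing the plan's figure.** Inputs from Sample size calculation: d = 0.40, 90% power, alpha 0.05 (taken as two-sided), 15% attrition.

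- Two-sample t test: 132 per group gives power 0.899; 133 gives 0.901. The stated 133 reproduces.
- 133 / (1 − 0.15) = 156.5, rounded up to 157 per arm; 2 × 157 = 314. The stated total reproduces.

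**Dilution.** Let f be the share of controls who already know the technique and practise it with full effect. The control mean then moves a fraction f of the way towards the acupressure mean, so the diluted effect is 0.40 × (1 − f). This ignores any change in the SD and assumes that attrition does not depend on earlier training. Power is for 133 analysed per arm.

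| Scenario | f | Diluted d | Power |
|---|---|---|---|
| No trained controls | 0 | 0.400 | 0.90 |
| Half of the 17 enrol, half of those go to control, half of those practise: 17 × 0.5 × 0.5 × 0.5 = 2.1 of 157 | 0.014 | 0.395 | 0.89 |
| All 17 enrol, split evenly, all in control practise fully: 8.5 of 157 | 0.054 | 0.378 | 0.87 |
| 10% of controls (assumed) | 0.10 | 0.360 | 0.83 |
| All 17 fall in control, an extreme: 17 of 157 | 0.108 | 0.357 | 0.83 |
| 20% of controls (assumed) | 0.20 | 0.320 | 0.74 |

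The halves in the second row are assumptions. The 10% and 20% rows would need trained people from outside the pilot, and the protocol gives no figure for how common earlier training is.

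**The case against.** **The criterion may already be strict enough.** Item 6 of the same list uses *ever* in the lifetime sense, for knee replacement. If the 6-month limit in item 8 belongs only to the steroid injection, acupressure is already barred for life. That reading is possible, though less natural. It stands as a reason to fix the wording, not as evidence that the gap is closed: it still would not settle whether self-administration counts.

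**Eligibility of the pilot trainees is not a fact.** A reader might infer that all 17 are eligible or will enrol. The documents do not support this. Entry depends on the conditions above, and no re-enrolment is planned or described.

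**Full dilution is unlikely.** On the window reading, an eligible trainee has gone more than 6 months without acupressure despite knee pain. Control reminders concern the health instructions, not acupressure. Assuming that every such person resumes with full effect is a worst case for the number enrolled. This stands, and it is why the moderate row is the better guide.

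**Controls would not have the full intervention.** The protocol was modified after the pilot, adding WhatsApp video and brief knee education. The active arm also gets checklists, acupressure reminders and a week-4 technique check. A trained control would have the technique, not the whole package. The refresher session and later check also show that the skill is treated as needing reinforcement.

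**Two further inferences fail.** Re-enrolled pilot participants would not carry planning data into the confirmatory result: they would be newly randomised with new baseline and outcome data, and nothing in the analysis section pools the pilot. Nor would earlier-trained people in the acupressure arm be uninformative about the course, since they would still attend both sessions and be checked. They would blur the answer, not void it.

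**Conclusion.** Exclusion 8 contradicts itself, leaves self-administration undefined and has no companion criterion for earlier training or pilot participation. People who already know the technique can therefore be eligible. This sits poorly with a design that keeps the training from controls until after the primary endpoint. Any resulting bias in the between-group NRS difference from trained controls runs towards no difference.

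The point is minor. From the pilot group alone, power falls from 0.90 to about 0.89 on moderate assumptions. It falls to 0.87 if all 17 enrol, split evenly and practise fully in control. The lower figures rest on assumed shares. A reader might infer that the trial is underpowered or its result compromised; the documents do not support that, and the planned 314 stands.

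**What to change.** Reword exclusion 8 in two parts and delete the conflicting *ever* from the time-limited part:

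- anyone trained at any time in self-administered acupressure for knee pain, including people in the acupressure arm of the pilot;
- anyone who, in the past 6 months, received acupressure for knee pain, self-practised it, or had a steroid injection for knee pain.

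The second part must name self-practice. If the window covered only acupressure given by a practitioner, a self-taught current user would be neither trained nor treated, and so would clearly be eligible.

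The cost is one screening question and a few otherwise eligible people not enrolled. No sample size or analysis figure changes.
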